### Statistical analysis

Statistical analysis on outcome measures will be conducted using Statistical Package for the Social Sciences (SPSS). First, data distribution will be assessed. Second, missing data will be handled by a multiple imputation technique. The primary analysis will be based on an intention-to-treat principle. Also, a per-protocol analysis will be performed as sensitivity analysis to assess the robustness of the results to protocol deviations [17]. The primary goal is to find a relation between the gait parameters (maximum peak load and step duration) and the discharge date. In addition, other spatiotemporal gait parameters measured by the SensiStep will be analyzed for this relation as well. The secondary goal is to find a relation between the gait parameters and the clinical measurements (i.e. EMS, FAC, and VAS). Relations between all data will be examined using multiple regression analysis.

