This trial is a two-arm, parallel-design, prospective RCT. Based on a previous pilot study, the average length of rehabilitation is 44 days, with a standard deviation of 17. Using a power of 0.80, an alpha of 5%, and an expected reduction of seven days (one week) in two-sided testing, a sample size of 94 participants per group was calculated. Participants will be allocated to either the control group or the intervention group using a stratified cluster randomization according to the sealed opaque envelope principle. First, all rehabilitation clinics were divided into two groups depending on the inclusion rate: < 2 vs. ≥ 2 eligible participants per month. This division was made to avoid skewing of inclusion rate in both arms. Then in both groups, clinics were randomized by the principal investigator into the control or intervention group using the sealed opaque envelope principle. This resulted in six rehabilitation clinics in the control group and five rehabilitation clinics in the intervention group (Table 1). Randomization per center, or cluster randomization, was chosen for two reasons. First, individual selection bias by the physical therapist is minimized. Second, and more importantly, the physical therapists and participants within one center can now provide a single treatment, either care as usual or care as usual, with real-time visual biofeedback. Considering the constant interaction between physical therapists, as well as between participants, individual randomization would increase the risk of data collection errors.

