### Participants

Strict inclusion criteria will be used to introduce homogeneity of the groups; therefore, participants enrolled in the study meet the following inclusion criteria:The participants rehabilitate from a proximal femur fracture following low energy trauma (e.g. fall from standing position).The participants have a prescribed unrestricted weight-bearing after (surgical) treatment of their fracture.The participants have an expected clinical rehabilitation duration of ≥ 2 weeks.The participants are aged ≥ 60 years.The participants have a bodyweight ≤ 120 kg.

Participants with the following criteria will be excluded from the study:People with cognitive impairment, defined as a score < 18 on the Mini Mental State Examination (MMSE) [16].People who are readmitted to the hospital within two weeks after study participation, for example for infectious complications.People with co-morbidities that affected gait significantly before the proximal femur fracture.

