### Outcome measures

The primary outcome measures are the gait parameters maximum peak load (in %bodyweight) and step duration (in seconds), which will be analyzed in relation to the discharge date from the rehabilitation center. It is expected that the intervention group will show an improvement in gait parameters and earlier discharge date compared to the control group. The discharge date will be determined by a multidisciplinary team within the usual institutional regime, irrespective of the study protocol. Secondary outcomes include other spatiotemporal gait parameters and validated clinical tests, including the EMS, the FAC, and the VAS. The EMS is a standardized validated scale for assessment of frail elderly people. The FAC is used as a diagnostic and evaluative tool to assess the physical performance of patients. The VAS is a commonly used, subjective scale to assess the amount of pain patients experience. Spatiotemporal gait parameters measured by the SensiStep will be correlated to the clinical test scores (e.g. EMS, FAC, and VAS). Blinding the participants and/or physical therapist is not possible, as both users are aware of the biofeedback they receive in the intervention group. However, data will be encrypted and anonymously delivered by the Steering Committee to the data scientists, which makes the data scientists blinded for the analysis of gathered data.

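### Recovery is measured over the rehabilitation stay with no stated role for time since surgery, which allocation of 11 clinics may leave unbalanced; prespecify the surgery-to-admission interval as a covariate.

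*Protocol article*

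**What the plan says.** All references are to the protocol article.

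- **Hypothesis (Background).** The intervention group is expected to reach higher peak loads and quicker steps earlier in rehabilitation, and to be discharged sooner.
- **Primary outcomes (Outcome measures).** Maximum peak load and step duration, "which will be analyzed in relation to the discharge date from the rehabilitation center". The Statistical analysis section makes this the main aim: "The primary goal is to find a relation between the gait parameters (maximum peak load and step duration) and the discharge date". The method named is multiple regression.
- **Sample size (Study design).** In the pilot, "the average length of rehabilitation is 44 days, with a standard deviation of 17". The calculation continues: "Using a power of 0.80, an alpha of 5%, and an expected reduction of seven days (one week) in two-sided testing", from which "a sample size of 94 participants per group was calculated".
- **Allocation (Study design).** Before clinics were randomised, "all rehabilitation clinics were divided into two groups depending on the inclusion rate". The outcome: "This resulted in six rehabilitation clinics in the control group and five rehabilitation clinics in the intervention group". Table 1 shows the same counts, and its only Swedish clinic is a control clinic.
- **Eligibility (Participants).** There is no limit on time since fracture or operation. One criterion reads: "The participants have a prescribed unrestricted weight-bearing after (surgical) treatment of their fracture".
- **Data recorded (Protocol).** Date of surgery and length of the rehabilitation admission are both documented, as additional participant information. The article gives date of surgery no part in the analysis.

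**The concern.** Recovery after a proximal femur fracture begins at the injury or operation, but this trial looks at it from the rehabilitation clinic onwards. Of two otherwise similar patients, the one admitted longer after surgery may walk better on the first rehabilitation day, and may need fewer rehabilitation days, with or without biofeedback.

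If the surgery-to-admission interval varies between clinics, it varies between the units that were allocated. The Discussion relies on 94 participants per arm to dilute patient differences, but for a factor that differs by clinic the relevant number is 11. Stratifying on inclusion rate does not address it. An imbalance could touch the gait outcomes and length of rehabilitation together, so agreement between them would not rule it out.

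**Working it through.** **1. The plan's own figure.** Inputs from Study design: difference 7 days, SD 17, two-sided alpha 5%, power 0.80.

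- Normal approximation: n = 2 × (1.960 + 0.842)² × 17² / 7² = 92.6, so 93 per group.
- Two-sample t-test: 93.55, so 94 per group. Power with 94 per group is 0.806 (normal approximation).

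The stated 94 reproduces, with patients treated as independent. The corresponding standard error of the arm difference is 17 × √(2/94) = 2.48 days.

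**2. How far 11 clinics can leave the interval unbalanced.** The documents give no acute-stay figures, so the between-clinic SD of the interval, *s*, is an assumption, shown as a range. With 6 versus 5 clinics of equal weight, the chance difference between arms has

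SD = *s* × √(1/6 + 1/5) = *s* × 0.606.

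Full transfer means that each extra day before admission replaces one rehabilitation day. Half transfer is half a day per day. Both rates are also assumptions.

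| Assumed *s* (days) | SD of arm difference, full transfer (days) | 95% range (days) | SD as share of 7 days | SD at half transfer (days) |
|---|---|---|---|---|
| 1 | 0.61 | ±1.2 | 9% | 0.30 |
| 2 | 1.21 | ±2.4 | 17% | 0.61 |
| 3 | 1.82 | ±3.6 | 26% | 0.91 |
| 4 | 2.42 | ±4.7 | 35% | 1.21 |

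**3. Whether the interval can be obtained.** The rehabilitation admission date is the discharge date minus the length of admission. The interval is that date minus the date of surgery. The first input is needed for the primary outcome, and the other two are on the list of documented items. The admission date is fixed before biofeedback starts, so the interval is a legitimate baseline value even though it is recovered from the discharge date.

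**4. Whether the gait time axis has to change.** For each measurement, days since surgery = interval + rehabilitation day. Take a linear model

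gait = b0 + b1 × rehabilitation day + b2 × interval + b3 × arm.

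Substituting rehabilitation day = days since surgery − interval gives

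gait = b0 + b1 × days since surgery + (b2 − b1) × interval + b3 × arm.

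The arm coefficient b3 is the same. Once the interval is in the model, changing the axis only reparametrises it.

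**The case against.** The strongest case against the point has five parts.

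- **No time origin is fixed.** The article ties gait to discharge but does not say that days are counted from rehabilitation admission. Regression with the surgery date as a covariate fits what is written, and covariates may be listed in a document not shown. This stands: a missing covariate list is not the finding. What remains is that the hypothesis, sample size and primary outcome are all framed on the rehabilitation stay, under a design that leaves a plausible pre-treatment difference uncontrolled.
- **The imbalance is speculative.** A reader might infer that differences in prior stay do shift the results, or that arms differ by 2 to 3 days, which would be 29% to 43% of the 7-day target (2/7 and 3/7). The documents support neither. For 2 to 3 days to be a one-SD event, *s* would have to be about 3.3 to 5.0 days (2/0.606 and 3/0.606). Even the direction is open: a patient transferred late because of complications might need more rehabilitation.
- **Clinics were randomised, so any imbalance is chance and not systematic bias.** This is correct. But the allocation has been made, and a chance imbalance in it would stay in the estimate.
- **The underlying matter is clustering.** With patients analysed as independent, *s* of 1 to 4 days and full transfer, two-sided type I error would be 5.7% to 16.1%. A reader might attribute this to the time reference, but it measures ignored clustering. A clinic-level error term would put the variation into the standard error. It would not remove a realised difference from the estimate, which the covariate can reduce.
- **Rehabilitation start is a sensible origin.** Biofeedback starts in the clinic. This stands, and step 4 of the working shows that no change of axis is required.

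**Conclusion.** The concern holds as a risk of unknown size, with an inexpensive safeguard. The trial measures faster recovery over the rehabilitation stay. Neither eligibility nor stratification controls time since surgery, and 11 allocated clinics cannot be relied on to balance it.

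Under the assumed between-clinic SD of 1 to 4 days, the chance arm difference in length of rehabilitation has SD 0.6 to 2.4 days at full transfer and 0.3 to 1.2 days at half, against a 7-day target. This rests on three assumptions: that the interval differs between clinics, that it affects gait or remaining stay, and that clinics carry roughly equal weight. The documents neither confirm nor exclude the first two. The effect on peak load and step duration cannot be quantified from the article.

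A reader might go further and infer that the only Swedish clinic being a control clinic biases the comparison. It does place any country difference in one arm, but the article reports no such difference. Nor does the article show that participants without surgery are enrolled; the brackets in the weight-bearing criterion only leave that possible.

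**What to change.** Keep the rehabilitation-based outcomes and add a sentence to the analysis along these lines: *The between-arm comparisons of maximum peak load, step duration and length of rehabilitation will be adjusted for the number of days from surgery to rehabilitation admission, as a baseline covariate, in a model that accounts for clinic.*

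For any participant treated without surgery, count from the date of fracture or of hospital admission, and state in advance which of the two is used. Presenting gait against days since surgery is optional.

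The cost is one model term. Date of surgery, discharge date and length of admission are already available; one extra date is needed only for non-surgical participants. Reporting the interval by clinic and arm in the baseline table would also show readers how large any imbalance was.

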**Methods:**

This is a two-arm, parallel-design, prospective, randomized controlled trial. Inclusion criteria are age ≥ 60 years, a proximal femur fracture following low energy trauma, and unrestricted-weight bearing. Exclusion criteria are cognitive impairment and limited mobility before trauma. Participants are randomized into either the control group, which receives care as usual, or the intervention group, which receives real-time visual biofeedback about weight-bearing during gait in addition to care as usual. Spatiotemporal gait parameters will be measured in 94 participants per group during a 30-m walk with an ambulatory biofeedback system (SensiStep). The progress of rehabilitation will be evaluated by the primary outcome parameters maximum peak load and step duration in relation to the discharge date. Secondary outcome parameters include other spatiotemporal gait parameters in relation to discharge date. Furthermore, the gait parameters will be related to three validated clinical tests: Elderly Mobility Scale; Functional Ambulation Categories; and Visual Analogue Scale. The primary hypothesis is that participants in the intervention group will show improved and faster rehabilitation compared to the control group.

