### Protocol

Data will be gathered according to a strict study protocol (Fig. 1). Candidate patients who fulfill the inclusion criteria will be asked to participate in the study by the site investigator and receive an information letter with the study protocol and study objectives. If patients agree to participate in the study, informed consent will be signed and the cognitive score will be evaluated by the MMSE. The MMSE is an objective score to quantitatively asses the severity of cognitive impairment. A MMSE score < 18 indicates severe cognitive impairment [16] and this leads to exclusion of the patient in this trial. After informed consent and MMSE, data will be collected from participants according to the following trial protocol. The institutional protocol for physical therapy after proximal femur fractures will be followed in all participants. In addition, each participant receives daily force measurements using the SensiStep system in a 30-m walk to measure the gait parameters. Additional clinical tests will be executed to gain additional insight in the rehabilitation progress of each participant:Functional Ambulation Categories (FAC, once per week)Elderly Mobility Scale (EMS, twice per week)Visual Analogue Scale (VAS, daily)

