## Discussion

The worldwide incidence of hip fractures among the elderly will increase due to the ageing population [1]. As hip fractures have a high morbidity and mortality, improvements should be made in the treatment of hip fractures. Biofeedback system have previously shown their potential, as weight-bearing significantly improved in partial and full weight-bearing [9]. This could improve fracture healing through mechanotransduction [6]. As stated before, the hypothesis is that real-time visual biofeedback results in a significant improvement in weight-bearing in the elderly after proximal femur fractures, especially with respect to the gait parameters maximum peak load and step duration, compared to standard training methods. Second, it is hypothesized that improvements in spatiotemporal gait parameters will lead to improvements in clinical scores, such as the EMS, FAC, and VAS. The aim of our trial is to validate these hypotheses and investigate the effect of real-time visual biofeedback on weight-bearing during the rehabilitation after proximal femur fractures in the elderly. This potentially leads to improved rehabilitation (e.g. better functional outcome), faster rehabilitation, and lower medical costs.

Although extensive attention has been paid to the study design, some difficulties still remain. One of the difficulties in this trial is the study population. Often, the elderly who sustain a hip fracture due to low energy trauma have (multiple) co-morbidities that could negatively affect gait. It is difficult to detect the amount of influence of these co-morbidities on gait. The question arises if any improvements or deterioration in gait is caused by real-time visual biofeedback or by the co-morbidities. To overcome this issue, the strict inclusion criteria for participants should minimize variability in the data. Moreover, the large number of participants (e.g. 94 per arm) should minimize the effect of co-morbidities on gait.

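### The stated primary analytic goal is an association between gait and discharge date; no intervention-versus-control contrast is specified for a between-arm hypothesis and sample size

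*Protocol article*

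**What the plan says.** All references are to the protocol article.

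**Hypothesis (Abstract, Methods).** "The primary hypothesis is that participants in the intervention group will show improved and faster rehabilitation compared to the control group". The end of the Background and the Discussion repeat the comparison with control or standard training: higher peak loads, shorter step durations and earlier discharge.

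**Sample size (Study design).** Mean length of rehabilitation 44 days, SD 17, an expected reduction of seven days, two-sided 5% alpha and power 0.80, giving 94 participants per group. The same section says that clinics were randomised, six to control and five to intervention.

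**Outcome measures.** Maximum peak load and step duration are the primary outcomes, "which will be analyzed in relation to the discharge date from the rehabilitation center". The between-group difference appears as an expectation: "It is expected that the intervention group will show an improvement in gait parameters and earlier discharge date compared to the control group".

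**Statistical analysis.** "The primary goal is to find a relation between the gait parameters (maximum peak load and step duration) and the discharge date". The next goal is of the same kind: "The secondary goal is to find a relation between the gait parameters and the clinical measurements (i.e. EMS, FAC, and VAS". The method is one sentence: "Relations between all data will be examined using multiple regression analysis". The section also says that the primary analysis follows intention-to-treat, with a per-protocol sensitivity analysis. No sentence in it names treatment group as a factor or defines a difference between arms.

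**The concern.** The trial asks whether biofeedback improves gait and brings discharge forward. The stated primary goal asks whether gait and discharge date are related. These are different questions, and an answer to the second does not answer the first.

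Gait is measured during rehabilitation ("each participant receives daily force measurements using the SensiStep system in a 30-m walk to measure the gait parameters"), and discharge comes at its end, so both follow allocation. If patients who walk better tend to leave sooner whichever clinic treats them, the relation will be found even when biofeedback does nothing. Conversely, biofeedback could shorten the stay while gait and stay are only weakly related.

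At stake is the trial's headline conclusion. Followed literally, the primary goal could be reported as met with an ineffective intervention. The comparison that the sample size was calculated for would also have no pre-stated form, leaving outcome, time point and model open to choice after the data are seen.

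**Working it through.** **1. Which comparison does the sample size belong to?**
Inputs from Study design: difference 7 days, SD 17, two-sided alpha 0.05, power 0.80, equal groups.
- Normal approximation: n per group = 2 × (1.960 + 0.842)² × (17/7)² = 92.6, rounded up to 93.
- Two-sample t-test: 93.55, rounded up to 94, the stated figure. Power at 94 per group is 0.802.

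So 94 per group is the sample size for a two-arm comparison of mean length of rehabilitation, before any allowance for clustering.

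**2. The sections side by side**

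| Section | Target |
|---|---|
| Abstract; Background; Discussion | Intervention versus control: gait and speed of recovery |
| Study design (sample size) | Intervention versus control: length of rehabilitation |
| Outcome measures | Gait in relation to discharge date; arm difference given as an expectation |
| Statistical analysis | Gait in relation to discharge date; gait in relation to clinical scores; no arm contrast |

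**3. How readily is the relation found with no treatment effect?**
The documents give no gait-stay correlation r, so a range is assumed. With 2 × 94 = 188 participants treated as independent, the Fisher approximation has standard error 1/√(188 − 3) = 1/13.60. Power is approximately Φ(13.60 × atanh|r| − 1.96), plus a negligible second tail.
- |r| = 0.1: 13.60 × 0.1003 = 1.36; power about 28%
- |r| = 0.2: 13.60 × 0.2027 = 2.76; power about 79%
- |r| = 0.3: 13.60 × 0.3095 = 4.21; power about 99%
- |r| = 0.5: 13.60 × 0.5493 = 7.47; power about 100%

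An observed correlation of about tanh(1.96/13.60) = 0.14 is enough for significance.

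**4. Simulation of both analyses** (4,000 trials per row, 94 per arm, bivariate normal data, no clustering, correlations assumed)

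| Scenario | Gait-discharge relation significant | Arm comparison of stay significant |
|---|---|---|
| No arm effect, r = -0.3 | 99% | 5.6% |
| No arm effect, r = -0.5 | 100% | 4.9% |
| 7-day reduction; gait unaffected and unrelated to stay | 5.3% | 81% |
| 7-day reduction and a 0.41 SD gait gain; otherwise unrelated | 8.8% | 79% |

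The last row can be checked by hand. The arm shifts are 0.41 SD in gait and 7/17 = 0.412 SD in stay. With half the participants in each arm, the covariance that they induce has size 0.25 × 0.41 × 0.412 = 0.042. Dividing by the pooled SDs, √(1 + 0.25 × 0.41²) × √(1 + 0.25 × 0.412²) = 1.04, gives a correlation of size about 0.04. Then 13.60 × 0.04 = 0.55, and the two tails give a power of about 8.5%, in line with the simulated 8.8%. A real effect on both outcomes thus barely registers in the pooled association.

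**The case against.** **Intention-to-treat implies a comparison by arm.** This largely stands. A reader might infer that the randomisation goes unused; the documents do not support that. The intention-to-treat and per-protocol statements only make sense by allocated arm, an arm difference is expected under Outcome measures, and the regression sentence does not exclude an arm term. What remains is that the contrast is implied and not defined, while a different target is explicitly ranked primary.

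**An article leaves model detail to the full protocol or analysis plan.** True of covariates and model form. It does not help here, because the article does state the primary analytic goal, and that goal does not match its own hypothesis or sample size.

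**Describing gait is a declared aim.** This stands. The abstract's Discussion paragraph lists normal gait patterns as the first aim and the biofeedback effect as the second. A gait-discharge regression has a legitimate place in the trial, but not as the test of the primary hypothesis.

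**The gait-score goal matches a stated hypothesis.** This also stands: "it is hypothesized that improvements in spatiotemporal gait parameters will lead to improvements in clinical scores". It would be wrong to call that goal misdirected for lacking an arm term. The regression alone would still not show that gait gains cause better scores.

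**Two stronger readings.** A reader might infer that the plan adjusts the arm effect for gait, a possible mediator, or that it aligns gait on the discharge date, an outcome that the intervention is meant to change. Neither analysis is stated, and the phrase about relation to discharge is ambiguous. The mediator point belongs only in the fix, as something to avoid.

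**Conclusion.** The point holds in this form: the Statistical analysis section ranks an association between two post-allocation outcomes as the primary goal and specifies no intervention-versus-control contrast, although the hypothesis and the 94 per group are both between-arm. It must be corrected, because that association can be significant with no biofeedback effect and can be missed when the full seven-day effect is present.

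The logic rests on the document's own wording and needs no assumed figure. The percentages do: they depend on the chosen correlations and ignore clustering, so they illustrate direction and do not estimate the size of the problem in this trial.

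**What to change.** 1. State as the primary analysis the intervention-minus-control difference by allocated arm, allowing for clinic as the randomised unit.
2. Apply it to the named gait outcomes, peak load and step duration, for example as arm-by-time from admission in a longitudinal model, and to length of rehabilitation, on which the sample size is based. A single fixed day is less safe, because the eligibility criterion of at least two weeks concerns the expected stay and does not guarantee a measurement on that day.
3. Say which of these outcomes is primary, so that Study design, Outcome measures and Statistical analysis agree. That choice is the sponsor's; length of stay should not silently replace the gait outcomes.
4. Put no post-allocation gait variable into the arm comparison as a covariate. If gait carries part of the effect, adjusting for it removes that part.
5. Compare EMS, FAC and VAS between arms as secondary outcomes.
6. Keep the gait-discharge and gait-score regressions as separate analyses of association, labelled non-causal, serving the descriptive aim.

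Cost: rewording of the objectives and analysis section, and a little more analysis of data already collected. Recruitment began in March 2017, so clarifying or changing the primary outcome is more than an edit. It should be dated, justified and made before anyone sees unblinded data.

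### The second hypothesis is causal (better gait leads to better EMS and FAC), but the only analysis stated for it is an association that frailty alone could make significant; no arm comparison of EMS or FAC is stated

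*Protocol article*

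**What the plan says.** Three parts of the protocol article bear on this point.

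- **Hypothesis (Discussion).** "it is hypothesized that improvements in spatiotemporal gait parameters will lead to improvements in clinical scores, such as the EMS, FAC, and VAS". The purpose follows: "The aim of our trial is to validate these hypotheses".
- **Outcomes (Outcome measures).** "Secondary outcomes include other spatiotemporal gait parameters and validated clinical tests, including the EMS, the FAC, and the VAS". The use made of the scores is "Spatiotemporal gait parameters measured by the SensiStep will be correlated to the clinical test scores (e.g. EMS, FAC, and VAS". The expected difference between arms in that section covers gait parameters and discharge date; it does not mention EMS or FAC.
- **Analysis (Statistical analysis).** "The secondary goal is to find a relation between the gait parameters and the clinical measurements (i.e. EMS, FAC, and VAS", with the method given as "Relations between all data will be examined using multiple regression analysis". No predictors, covariates or arm term are named.

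The Discussion also says that elderly hip fracture patients often "have (multiple) co-morbidities that could negatively affect gait", and that "It is difficult to detect the amount of influence of these co-morbidities on gait". It relies on strict inclusion criteria and on 94 participants per arm to deal with this.

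**The concern.** The hypothesis is that changing gait changes function. Its null is that improving gait does nothing for EMS or FAC. The stated analysis has a different null, that gait and score are unrelated. The two separate as soon as something else drives both quantities. Frailty and co-morbidity are the obvious candidates, and the article itself accepts that co-morbidities affect gait and are hard to disentangle. That they also lower EMS and FAC is an inference, though a modest one.

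A larger sample does not help. It leaves the confounding of an association in place and makes the confounded association easier to detect.

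EMS and FAC are the trial's functional scores, and the Discussion lists better functional outcome among the hoped-for gains. Followed as written, the text could declare the second hypothesis validated in a trial where biofeedback raised peak load and left function unchanged. Randomisation could expose that result, but no comparison of these scores between arms is stated.

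**Working it through.** **1. Sample size.** Inputs from Study design: SD 17 days, difference 7 days, two-sided alpha 5%, power 0.80. Normal approximation: n = 2 × (1.96 + 0.8416)² × 17² / 7² = 92.6, so 93 per group. The two-sample t-test needs 94 (power 0.802), which reproduces the stated figure. It concerns length of rehabilitation and serves here only to give N = 2 × 94 = 188.

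**2. Set-up.** One gait value and one score per patient. Frailty explains a share r of the variance of each, so the induced gait-score correlation is √r × √r = r. There is no path from gait to score and no biofeedback effect. The value of r is an assumption, shown as a range.

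**3. Rejection of the association test.** By Fisher's z the rate is Φ(√185 × atanh r − 1.96) + Φ(−√185 × atanh r − 1.96), where 185 = N − 3 and √185 = 13.60. For r = 0.20: 13.60 × 0.2027 = 2.757, and Φ(0.797) = 0.787. A simulation of 4,000 runs per setting, regressing score on gait and arm, agrees. The adjusted column adds a frailty proxy of reliability 0.5.

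| Induced r | Fisher z | Simulated | Simulated, adjusted for proxy |
|---|---|---|---|
| 0.05 | 10% | 10% | 7% |
| 0.10 | 28% | 28% | 11% |
| 0.15 | 54% | 54% | 20% |
| 0.20 | 79% | 79% | 33% |
| 0.30 | 99% | 99% | 67% |

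At r = 0.134 the formula gives about 45% (13.60 × 0.1348 = 1.834; Φ(−0.126) = 0.45). A sample correlation of tanh(1.96 / 13.60) = 0.143 is enough for p < 0.05. Adjusting for frailty measured without error brings the rate back to about 5%.

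**4. The proxy column by hand.** With reliability 0.5 the partial correlation is 0.5r / (1 − 0.5r). For r = 0.20 this is 0.10 / 0.90 = 0.111. Then √184 × atanh(0.111) = 1.51, and Φ(1.51 − 1.96) = 0.33.

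**5. Arm comparison on the same data.** Comparing the score between arms rejects in 4.6% to 5.5% of runs at every r. No clinic effect was simulated, so a real analysis needs a method that allows for clinics.

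**6. Biofeedback moves gait only.** Suppose biofeedback shifts gait by 0.41 SD (7/17, borrowed as an assumption) and does nothing to the score. The gait-score correlation rejects in 27%, 78% and 98% of runs at r = 0.10, 0.20 and 0.30. The arm comparison stays at about 5%.

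**The case against.** The best reply is that the article condenses a fuller plan. It says only multiple regression, so covariates, an arm term or a model of change would all fit the text. Co-morbidities, age, gender and walking aid are recorded. The scores are named secondary outcomes of a two-arm trial with an intention-to-treat principle. The causal wording is in the Discussion, and relating gait to validated scales is a legitimate descriptive aim.

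Much of this stands. A reader might infer that the plan fixes a regression of score levels on gait levels, or rules out an arm comparison. The documents say neither. What remains is that hypothesis, aim and analysis goal are all stated and do not match. A faithful elaboration of the stated goal would still answer a different question, and covariates help only as far as they capture frailty.

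Three stronger readings also fail.

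- **The test rejects whenever frailer patients do worse on both.** The no-association null is then false, but rejection depends on strength: 10% at r = 0.05 and 28% at r = 0.10. The exclusion of co-morbidities that significantly affected gait before the fracture, and of MMSE below 18, may narrow the shared frailty.
- **Rejection is near 95% to 100%.** At 20% to 30% shared between-patient variance, such figures come from pooling visits as if independent. Pooling alone gave 45% rejection with no shared variance. The article does not say visits will be pooled.
- **A within-patient change model would settle causation.** It removes only stable confounding. With no gait effect but recovery rates correlated between gait and EMS, such a model rejected in about 16% of runs (correlation 0.3, rate SD 0.5 per 44 days), 59% to 60% (0.3, SD 1.0) and 94% to 96% (0.5, SD 1.0). With rate SD 0.25 it stayed near 5% to 7%. These inputs are also assumptions.

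**Conclusion.** The point holds as a mismatch between a stated causal aim and a stated associational analysis, and it should be corrected. With no effect on function, false confirmation at N = 188 runs from about 10% to 99% as the induced correlation goes from 0.05 to 0.30. This assumes one record per patient, a stable shared cause and no adjustment. The documents give no value for that correlation, so no single rate can be claimed. The correlation analysis is sound as description; the fault lies in using it to validate a causal statement. The primary outcomes and the sample size are not affected by this point.

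**What to change.** 1. In Outcome measures and Statistical analysis, state a comparison of EMS and of FAC between intervention and control at a time fixed in advance, by intention to treat and with a method that allows for randomisation by clinic. The two-week assessment is one option, since inclusion requires an expected stay of at least that long. Any claim of better function should rest on this comparison.
2. Word its conclusion as the effect of biofeedback on function. It does not test the effect of gait on function.
3. Report the gait-score relation, including any within-patient change model, as descriptive only.
4. Remove the causal verb and the language of validation from conclusions that rest on that relation.

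Gait is measured daily, EMS twice weekly and FAC weekly, so no new data are needed; the cost is wording and one more analysis. The downside is a comparison made less precise by having 11 clinics (six control, five intervention), and a weaker claim about the gait-function link.
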